**3.9.1. Treatment with Topical MAL Photosensitizer**

Before the treatment, the treated area will be cleansed with 0.2% aqueous chlorhexidine. Following this, a light curettage will be performed on the facial area using a sterile curette.

After curettage, a thin layer of the photosensitizer, approximately 1 mm thick, will be applied to the affected areas of the participant's face. An occlusive dressing will then be applied to enhance the penetration of 8% or 16% MAL. This dressing will be covered with aluminum foil to protect from light, preventing ambient light from influencing the protoporphyrin production process.

**3.9.1.1. Conventional PDT Protocol**

For the conventional PDT technique, the dressing will remain on the face for a period of 1 hour for participants in G2 and G4 and 3 hours for participants in G1 and G3. Participants who request it will be discharged to their homes and asked to return to the clinic after the required incubation period (1 or 3 hours, depending on the protocol), allowing them to be treated on the same day.

After the proposed incubation period, the dressing will be removed, and the excess photosensitizer will be wiped off with gauze soaked in 0.9% saline before light exposure. The distance between the red narrow-spectrum LED (Light Emitting Diode) lamp and the skin will be approximately 1 cm. The LED device used will be the Hygialux LLT1601®, produced by KLD, São Paulo, Brazil. The parameters used were appropriately calculated.
The light source for skin illumination will be visible light (LED) with a wavelength of 643nm (ANVISA Registration No. 10245239012).

Table 1 – Dosimetric Parameters and Technique for Using the Photosensitizer

| **Parameter** | **Value** |
| --- | --- |
| Central Wavelength (nm) | 643 |
| Spectral Width (FWHM) (nm) | 20 |
| Mode of Operation | Continuous |
| Average Radiant Power per LED (mW) | 19 |
| Average Radiant Power (mW) | 22,169.2 |
| Polarization | Random |
| Beam Profile | Multimode |
| Beam Size on Target (cm²) | 465.6 |
| Irradiance on Target (mW/cm²) | 48 |
| Exposure Time (s) | 1,570 |
| Radiant Exposure on Target (J/cm²) | 75 |
| Radiant Energy per Session (J) | 34,805.6 |
| Application Technique | 1 cm distance from target |
| Session Frequency | 1 |
| Number of Sessions | 1 |
| Total Radiant Energy (J) | 34,805.6 |
| Photosensitizer | 8% MAL and 16% MAL |
| Pre-irradiation Time | 1 hour or 3 hours |

The energy per session is 75 J/cm², as instructed by the manufacturer (Metvix® package insert). This is considered the standard energy amount in the literature (Vignion-Dewalle, et al., 2017). All other calculations were based on this standard dose by a specialist physicist in this field ([name]). After the session, participants will be advised to avoid sun exposure for one week, and a sunscreen with a sun protection factor (SPF) of 30 in a creamy lotion will be prescribed. Free samples will be provided to the participants.

**Medication Treatment**

All participants will receive a prescription for pain management if needed:
• Paracetamol every 6 hours for 3 days, only if pain occurs.

Paracetamol is a potent non-opioid analgesic with central action, which will relieve pain when necessary. It is the preferred medication for treating mild to moderate pain, whether acute or chronic. It is effective and has a better safety profile compared to other non-opioid analgesics. In the United States, it is the most prescribed medication for acute pain. Studies show that paracetamol is effective in relieving postoperative pain. In a large study, about half of the patients who received paracetamol achieved at least 50% pain relief within 4 to 6 hours, compared to only 20% of those who received a placebo. This indicates that paracetamol works well for many people. The side effects of paracetamol (such as nausea, vomiting, and drowsiness) are generally mild to moderate and are more related to surgical procedures than to the medication itself (SACHS, 2005; TOMS, 2010).

If the participant is allergic to paracetamol, as indicated by anamnesis, dipyrone 500 mg every 6 hours can be prescribed as an alternative. Dipyrone, widely used in Brazil, has been banned in many European countries and the United States due to severe allergic reactions and the risk of agranulocytosis (a potentially fatal condition). However, studies show that dipyrone has similar efficacy to other non-opioid analgesics in relieving postoperative pain. A 2010 Cochrane review by Ramacciotti et al. revealed that an oral dose of 500 mg provided at least 50% pain relief in 70% of patients within 4 to 6 hours. Furthermore, dipyrone showed comparable efficacy to ibuprofen. In cases of tension headaches and migraines, dipyrone also proved effective. Although rare, its adverse effects are generally mild (EDWARDS, 2010).

In the last case, 400 mg of ibuprofen every 6 hours can be prescribed. In a study evaluating postoperative pain control, single doses of ibuprofen (200 mg and 400 mg) showed at least 50% pain relief compared to placebo. The use of more soluble ibuprofen salts was even more effective. Adverse events were rare and like the placebo (WAHBA, 2004).

Participants will be instructed to contact the physician and the principal investigator via mobile phone if necessary or if they have questions regarding the study. All participants will leave the clinic with the prescribed medication but will only take it if necessary in cases of severe pain that does not improve with the previously recommended medication:

• Toragesic® (Ketorolac Tromethamine) 10 mg every 6 hours (maximum dose for elderly over 65 – 40 mg/day).

**3.10. Study Outcomes**

The primary outcome variable of the study will be:

**• Complete remission** - Quantitative assessment: a count of lesions with a complete response will be performed, meaning those that show total disappearance after treatment. These lesions will be clinically evaluated at 30 days, 3, 6, and 12 months post-treatment, and the number of lesions at these time points will be compared to the baseline. Both absolute and relative lesion counts will be considered. To avoid variability in counting, only one researcher will conduct the counts. This researcher will be calibrated before the study begins. Complete lesion remission will be defined as 100% remission of lesions after 12 months of treatment, as Jansen et al. (2019) described.

The secondary outcome variables will be:

• **Treatment success** - Evaluation of the proportion of participants who show at least a 75% reduction in the initial number of actinic keratosis lesions in the treatment area after the last day. Assessments will be conducted at 30 days, 3, 6, and 12 months. Both absolute and relative lesion counts will be considered. Treatment success will be defined as complete remission in at least 75% of participants over 12 months, as Jansen et al. (2019) established.

**• Recurrence rate** - The recurrence rate of actinic keratoses will be defined as the reappearance of lesions in previously treated areas. Recurrence will be evaluated at the same follow-up periods, namely 30 days, 3, 6, and 12 months after treatment completion. Recurring lesions will be quantified, considering both absolute and relative numbers of lesions. These lesions will be monitored and re-treated at the end of the study unless malignancy is present, in which case they will be treated immediately.

At the end of the treatment, if lesion worsening is observed in any of the groups not treated with the gold standard (G1), which is unlikely given previous studies with lower concentrations and satisfactory results, or if the treated lesions recur in any group, a local procedure may be performed at no cost to the participant. This outpatient procedure, known as cryotherapy, is non-invasive but more destructive than the proposed treatment in this protocol. It involves the application of liquid nitrogen with the Cryac® device to freeze the lesion, resulting in its local destruction. The procedure may cause blistering and a mild, transient burning sensation and may leave some scarring. It will be performed in a specialty outpatient clinic or private clinic, with follow-up care as needed (BAKER, 2017).

• **Prevention of Squamous Cell Carcinoma (SCC)** - If lesion malignancy occurs during the follow-up period, the gold standard treatment, surgical intervention, will be applied. Participants will be continuously monitored to prevent the development of SCC in the treatment area throughout the study. Participants will remain in the study since follow-ups consist only of monitoring. Malignant lesions will be quantified, considering both absolute and relative numbers. The principal investigator will perform dermatoscopy at no cost to the participant, and if malignancy is suspected, the lesion will be excised in a procedure known as "minor surgery." This is a routine dermatological procedure performed on an outpatient basis, without sedation or hospitalization, using local anesthesia. The patient will be discharged on the same day. The surgery involves removing a small amount of skin tissue containing the lesion, suturing the skin to close the wound, and applying a dressing. Sutures should be removed within 7 to 10 days after surgery. The tissue removed during the minor surgery will be The specimen is placed in a formalin container provided by the laboratory and sent to a pathology laboratory for diagnostic confirmation. The procedure can be performed at a specialty outpatient clinic or private clinic. As expected with minor surgery, scarring and temporary pigmentation changes may occur, which will improve over time.

• **Incidence of adverse effects -** The incidence of adverse effects, such as erythema, edema, itching, and peeling, will be monitored through a personal diary kept by the participant, in which detailed descriptions of any adverse effects will be recorded. As Jansen et al. (2019) recommended, this method will allow participants to report their symptoms individually. The principal investigator, a dermatologist specializing in this type of treatment, will offer continuous assistance and follow-up, remaining accessible as needed.

• **Subjective pain assessment** - Subjective pain will be assessed using the Visual Analog Scale (VAS), consisting of a 10-mm line with closed ends, indicating "0" for no pain and "10" for unbearable pain, the worst pain ever felt. The same operator will consistently provide instructions for marking the scale. Each participant will be instructed to mark with a vertical line the point that best reflects the intensity of their pain at the time of assessment, following the guidelines of Bottega et al. (2010). These assessments will be conducted weekly for up to 30 days after treatment, followed by evaluations at 3, 6, and 12 months.

[figure not shown]

Figure X: VAS - Visual Analog Scale for Pain. Source: the author

**Rescue Medication**: Rescue medication will be assessed by the standardized amount of analgesics consumed (paracetamol). At the start of the study, each participant will receive a blister pack of paracetamol®, a drug with purely analgesic effects, as Jóźwiak-Bebenista (2014) recommended. Participants are instructed to keep the blister pack until the end of the experiment and bring it to each appointment. At the end of the study, the number of tablets used will be evaluated in each group as a pain measurement parameter. In cases of reported allergy during anamnesis, dipyrone or ibuprofen may be prescribed as alternatives (WAHBA, 2004; TOMS, 2010).

• **Evaluation of Skin Texture, Wrinkles, and Pigmentation**: This evaluation will be conducted at 30 days, 3, 6, and 12 months, using the scale by Tina Alster et al. (2005). This scale, assessed by professionals and participants, classifies improvements as minimal (<25%), moderate (25%-50%), significant (51%-75%), and excellent (>75%). These evaluations will provide a comprehensive approach to measuring the effectiveness of the treatment over time.

Participant Satisfaction – This will be assessed using the Actinic Keratosis Quality of Life questionnaire (AKQoL) (Esman et al., 2013) after 6 months and 1 year of treatment. The items will be scored on a standard 4-point Likert scale and summarized into a maximum score of 32 points. A higher score indicates greater impairment in quality of life. The questionnaire has been translated and validated into Portuguese (Vilhena et al., 2022).

EVALUATION OF SATISFACTION WITH FACIAL APPEARANCE (FACE-Q)

The FACE-Q scale (Satisfaction with Facial Appearance Overall) was developed by Klassen (Klassen et al., 2010) and consists of 10 items to be answered using a four-point Likert scale, which measures satisfaction with facial appearance in various scenarios. A Likert scale consists of a set of items in which the subject being evaluated is asked to indicate their level of agreement, ranging from "strongly disagree" (level 1) to "strongly agree" (level 4). The FACE-Q evaluates the perception of facial appearance in terms of characteristics such as symmetry, harmony, proportion, freshness or vitality, temporal appearance (e.g., rested facial appearance, at the end of the day, or upon waking), appearance under brighter lighting, appearance in photographs, and profile (lateral view or contour of the face). Despite being recent, the scale has already been used in several studies (Chang et al., 2016; Sinno et al., 2015; Kappos et al., 2017). Its adaptation to Brazilian Portuguese was carried out by Gama in 2018. The FACE-Q scale, validated for use in Brazil (Table 6), consists of nine items that measure two satisfaction factors (Overall facial appearance and Facial geometry). The item "With the appearance of your face at the end of the day" from the original scale was removed in the Brazilian version due to its low representativeness in the Brazilian sample, and for calculation purposes, it was also excluded from the evaluation in the present study. The sum of the scores obtained from patients' responses to the 9 items (1 = very dissatisfied, 2 = somewhat dissatisfied, 3 = somewhat satisfied, and 4 = very satisfied) can range from 9 to 36 and are converted into a score ranging from zero to 100. Higher scores indicate greater satisfaction (Table 7). The participants answered the FACE-Q questionnaire adapted to Brazilian Portuguese (Appendix C) before treatment and 30 days after its completion.

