Classically, participants can be classified into four subgroups according to the extent of the disease to define the best therapeutic modality to be used: participants with single lesions (<5 lesions per body area), with multiple lesions (six or more lesions per body area), those with cancerization field areas, and immunosuppressed participants (Werner et al., 2015).

Therefore, treatments for actinic keratoses are indicated for aesthetic reasons, to relieve associated symptoms, or to prevent the development of skin cancer. Detectable lesions are often associated with alterations in the surrounding skin where subclinical lesions may be present. Available interventions include individual lesion-based treatments or field-targeted treatments. These may vary in efficacy, safety, and cosmetic outcomes (Steeb et al., 2019).

Therapeutic alternatives are divided into four categories: topical drug treatment with ingenol mebutate, hyaluronic acid gel diclofenac, 5-fluorouracil, imiquimod, resiquimod, and masoprocol; oral retinoids; chemical treatments including cryotherapy with liquid nitrogen, photodynamic therapy, chemical peels (medium or deep depth), and dermabrasion; and mechanical treatments involving non-ablative laser resurfacing (1927nm fractional thulium fiber) and ablative laser resurfacing with carbon dioxide (CO2) and Erbium

(Friedman et al., 2012; Heppt et al., 2020; Jansen et al., 2020).

Using these methods in combination or sequence is a common practice in the approach to these participants. Treatment choice varies according to the clinical presentation, location, number, and extent of lesions; therefore, care should be individualized according to each participant’s needs (Campione et al., 2022).

Overall, 25% to 75% of participants treated require retreatment within twelve months due to the appearance of new lesions, denoting the chronic nature of this condition, even when cancerization field treatment has been performed. The worst recurrence rates are observed in participants treated only with cryotherapy, and the lowest recurrence rates are observed in those who underwent cancerization field treatment (Bakos et al., 2013; Reinehr; Bakos, 2019).

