**2.2. Specific Objectives**

**•** To evaluate complete remission (100% remission) of the lesions in relation to the initial number of facial lesions at 3 months (primary objective);

• To evaluate complete remission (100% remission) of the lesions in relation to the initial number of facial lesions at other time points: 30 days, 9 months, and 12 months;

• To evaluate treatment success (75% reduction in the initial number of lesions in the treatment area compared to baseline) at 30 days, 3, 6, and 12 months;

• To evaluate the recurrence rate (reappearance of lesions in previously treated areas) at 30 days, 3, 6, and 12 months;

• To prevent squamous cell carcinoma (conduct assessments to verify the occurrence of squamous cell carcinoma. Cases will be recorded and treated as necessary. Evaluations will be carried out at 30 days, 3, 6, and 12 months);

• To evaluate the incidence of adverse effects through participants’ self-completed diaries and researcher notes. Assessments will be conducted at 30 days, 3, 6, and 12 months;

• To assess postoperative pain, if it occurs, after treatments using the visual analog scale (VAS) at 0 days, 30 days, 3, 6, and 12 months;

• To evaluate the amount of analgesics consumed weekly during the first week after treatment;

• To assess improvements in skin texture, wrinkles, and pigmentation using the scale by Tina Alster et al. (2005) at 30 days, 3, 6, and 12 months;

• To assess participants' quality of life using the Actinic Keratosis Quality of Life questionnaire (AKQoL) (Vilhena et al., 2022) after 6 months of treatment;

• To assess participants' quality of life using the Face-Q questionnaire (Klassen et al., 2015) after 6 months of treatment.

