**3.7. Avaliações pré-tratamento**

After receiving the necessary explanations, participants affected by actinic keratosis who sign the Informed Consent Form (ICF) will undergo anamnesis and complete the AKQoL and Face-Q questionnaires, as well as the data collection form for the study, which will involve counting, classifying, and mapping the facial lesions. These data will be collected by the principal investigator (calibrated). Photographic records of the lesions will also be taken using a Quantificare® 3D camera and the camera of an iPhone 11 Pro Max. Following these evaluations, the treatment will be conducted according to the randomization.

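### Recurrence is defined by treated area, with no prior clearance and no denominator, so new or never-cleared lesions can score as recurrences; the remission wording leaves open whether new lesions count.

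*Protocol*

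**What the plan says.** **Recurrence (Protocol 3.10, secondary outcome).** The definition is: "The recurrence rate of actinic keratoses will be defined as the reappearance of lesions in previously treated areas". The timing is: "Recurrence will be evaluated at the same follow-up periods, namely 30 days, 3, 6, and 12 months after treatment completion". The metric is: "Recurring lesions will be quantified, considering both absolute and relative numbers of lesions". No denominator is given for the relative number. Section 2.2 repeats the area-based wording and the day-30 visit.

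**Complete remission (Protocol 3.10, primary outcome).** The text first describes a tally of treated lesions: "a count of lesions with a complete response will be performed, meaning those that show total disappearance after treatment". It then says that "the number of lesions at these time points will be compared to the baseline", without saying whether a lesion absent at baseline enters the later number. Section 2.2 speaks of "complete remission (100% remission) of the lesions in relation to the initial number of facial lesions at 3 months (primary objective".

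**Baseline map (Protocol 3.7).** Pre-treatment data collection includes "counting, classifying, and mapping the facial lesions", with photographs. No section says how the map is used at follow-up or how a new lesion is classed.

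**Background (Protocol, Contextualization).** "Overall, 25% to 75% of participants treated require retreatment within twelve months due to the appearance of new lesions".

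**The concern.** Recurrence is something that happens to a lesion: it was present, it cleared, it came back. The rule in 3.10 is tied to an area and lacks the middle step. Three consequences follow.

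- A new lesion in the treated field satisfies the wording. The cream goes on the affected areas of the face (3.9.1), and the protocol's own background describes new lesions as common.
- At day 30 no earlier lesion assessment has established clearance, so a lesion that persisted cannot be told from one that cleared and returned.
- Only cleared lesions can recur. The absolute number therefore has a risk set that grows with efficacy, and an arm that clears more can show more recurrences at the same underlying risk.

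The primary outcome has a related gap. If the number of lesions at a visit includes new ones, a participant whose treated lesions have all gone can still fail complete remission. Two readings of a primary outcome should not be left open, because the examiner must record whether a lesion is old or new at the visit. Bare counts will not yield it later.

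**Working it through.** **1. The plan's own figure.** Inputs from 3.1: 64% and 91%, 5% level (two-sided assumed), 80% power, 36 per group. Pooled formula:

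n = [1.960·√(2·0.775·0.225) + 0.842·√(0.64·0.36 + 0.91·0.09)]² / 0.27² = 36.3 per group, or 37 rounded up.

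Power at 36 = Φ[(0.27·√36 − 1.960·√0.34875) / √0.3123] = 79.6%. The stated 36 is reproduced to within one participant.

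**2. Absolute recurrences at equal risk.** Assume 5 lesions per participant (the inclusion minimum in 3.4), so 36 × 5 = 180 per arm, and a 20% recurrence risk among cleared lesions in both arms. Clearance is set at the two planning rates.

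| | 91% cleared | 64% cleared |
|---|---|---|
| Cleared | 180 × 0.91 = 163.8 | 180 × 0.64 = 115.2 |
| Recurred | 163.8 × 0.20 = 32.8 | 115.2 × 0.20 = 23.0 |
| Never cleared | 16.2 | 64.8 |
| Present at the end | 49.0 | 87.8 |

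The better arm shows 33 recurrences against 23 while carrying far fewer lesions. The ratio, 0.91/0.64 = 1.42, does not depend on the assumed 20%.

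**3. The same arithmetic on the rates the protocol cites.** The Contextualization section reports, from the earlier study of incubation time and concentration, complete response of 85%, 76%, 77% and 74%. It reports 12-month lesion recurrence of 17% and 19% for 16% MAL and 44 to 45% for 8% MAL. (The text calls the last figure lower, against its own numbers; the figures are used here.)

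| Arm | Cleared of 180 | Recurrence rate | Raw recurrences |
|---|---|---|---|
| G1 (16%, 3 h) | 153.0 | 17% | 26.0 |
| G2 (16%, 1 h) | 136.8 | 19% | 26.0 |
| G3 (8%, 3 h) | 138.6 | 44–45% | 61.0–62.4 |
| G4 (8%, 1 h) | 133.2 | 44–45% | 58.6–59.9 |

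The concentration contrast survives in raw counts. The 17% versus 19% contrast vanishes. These response rates followed one or two treatments, whereas this trial gives one session, so they are a guide only.

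**4. Remission if new lesions count.** Let q be the share of participants with a new lesion, equal across arms and independent of clearance. Take 25% to 75% from the background, and read the planning rates as participant-level rates. Each rate becomes p(1 − q), and power follows from the formula in step 1.

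| q | Rates | Difference | Power at 36 |
|---|---|---|---|
| 0 | 64% vs 91% | 27.0 points | 79.6% |
| 25% | 48% vs 68% | 20.3 | 41% |
| 50% | 32% vs 46% | 13.5 | 21% |
| 75% | 16% vs 23% | 6.8 | 11% |

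**5. Sensitivity of step 4.** In 3.1 the planning rates are lesion responses at 3 months. If instead each participant has 5 independent lesions, participant clearance is 0.91⁵ = 62% and 0.64⁵ = 11%. The same formula then gives power of 99.9%, 97%, 82% and 48% for q = 0, 25%, 50% and 75%. Independence is extreme in the other direction. Power falls under both readings, but by very different amounts.

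**The case against.** The best case for the plan runs as follows.

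- **The intent is visible.** Reappearance suggests a lesion that had gone, and the cryotherapy text in 3.10 speaks of treated lesions recurring. This shows what was probably meant. It does not repair the operative definition, which names areas, omits clearance and includes day 30.
- **Relative numbers are also named, and no between-arm test of absolute recurrences is specified.** This stands. The plan does not rely on raw counts alone; the defect on the relative side is the missing denominator.
- **The remission text points to treated lesions.** A reader might infer that the protocol counts new lesions as remission failures. It does not say so. The sentence on total disappearance, the reference in 2.2 to the initial number and the baseline map all lean the other way; only the comparison of visit numbers with baseline admits new lesions.
- **A real difference is not generally hidden.** A reader might infer from step 2 that it is. Step 3 shows otherwise for concentration on the cited rates.
- **The power series is fragile.** It uses 3-month lesion rates as if they were 12-month participant rates. It also borrows a range for retreatment after actinic keratosis treatments in general, which is not specific to new lesions in this treated field. This stands.
- **Field clearance is a legitimate outcome.** The protocol credits photodynamic therapy with a potential to prevent new lesions, so excluding them from remission is partly a choice of what to estimate. This also stands; the plan needs to fix one reading and report the other.

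**Conclusion.** The concern holds for recurrence, and holds as an ambiguity for remission. Followed literally, the recurrence rule can score new lesions and lesions that never cleared as recurrences. Its absolute version is inflated in the arm that clears more, by a factor of 1.42 at the planning rates (33 against 23 per 180 lesions at an assumed equal 20% risk). The practical damage is bounded: recurrence is secondary, and on the cited rates the 16% versus 8% contrast stays visible (about 26 against 59 to 62).

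For the primary outcome, the documents do not support saying that new lesions are failures by rule, nor a firm figure for lost power. They support saying that the wording permits two readings and that, under the one including new lesions, power could fall well below 80%. How far depends on the unit of the planning rates, on q, and on its independence from clearance.

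These calculations also assume 5 lesions per participant and use lesion counts without allowing for clustering within participants. The wording should be corrected because outcome definition and visit recording both depend on it.

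**What to change.** - At every visit, use the baseline map to score each mapped lesion as clear, persisting or recurred. Record new lesions as a separate outcome.
- Define recurrence as a mapped lesion clear at 3 months and present at 6 or 12 months. Report it descriptively over lesions clear at 3 months, since that group is selected after randomisation.
- Drop the day-30 recurrence assessment and the absolute recurrence number as a between-arm comparison.
- Compare durability as the proportion of all randomised participants with every mapped lesion clear at both 3 and 12 months.
- State in the primary outcome that complete remission refers to the mapped baseline lesions, in line with section 2.2, and report field clearance including new lesions alongside.

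No new visits or equipment are needed, because lesions are already mapped and photographed before treatment. The cost is lesion-level recording at each visit and some uncertainty in telling a recurred lesion from an adjacent new one: the protocol notes that borders are often poorly defined, and the calibration in 3.2 covers lesion number only. The durability comparison is an added endpoint and should be labelled as secondary.
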